#### Data management {19}

The PI and study personnel will be responsible for managing data collection. As this is an Internet-based trial, the participants will complete assessments individually, with their data entered directly into REDCap. Administered surveys will predominantly collect quantitative data. Dried blood spot samples will be analyzed at a biochemical laboratory affiliated with the University of Toronto.

Data for this study will be managed using REDCap electronic case report forms. This system is maintained on central CAMH servers, with data backed up daily, and is supported by the Research Informatics department. Access to study data will be limited to the PI and primary research team members. In order to ensure that participant information is only accessible to approved members of the study team, REDCap permissions to access the project data will only be provided to the users who need to access the data for study conduct or monitoring purposes. A data dictionary (and any other necessary supporting documentation) will be created and saved along with the datasets, so that others can understand the variables and data structure.

Once data collection is complete, the data will be backed up on a CAMH server to a folder with limited access, and the necessary supporting documentation will be saved along with the files. Only the PI, and other members of the study team who require direct access to the data for data management and/or analysis, will be given permission to access this folder.

The PI will retain all study data for a period of at least 10 years as per CAMH policy for unregulated studies.

#### Confidentiality {27}

Personal identifying information will only be collected once at the time of enrollment for the purposes of mailing study intervention supplies to participants and communicating survey invitations via email or text, depending on participant preference. Each randomized participant will be assigned a unique identifier that will be used to link all the questionnaires for that participant. The personal identifying information will be kept separate from the participant data. Materials used to mail back dried blood spot collections for testing, and test results, will be labeled with a participant identification number only and not with any personal identifying information. For daily diary and weekly questionnaires, participants will be given the option to receive SMS text messages via Twilio. Twilio is a widely used third-party SMS provider integrated with the REDCap platform. Phone number and mailing address are kept separately from other participant information and are accessed from a de-identified record by Twilio and study team to send SMS and mail out the study packages, respectively.

After data collection is complete, the data will be exported from REDCap in csv file format, to permit data analysis, sharing, and storage on CAMH’s secure Y-drive. A single master .csv file with personal identifying information will be saved separately from a single master .csv file with all de-identified study data. Master files will not be used for analysis to minimize the risk of data being improperly or erroneously overwritten or modified. A copy of the master de-identified file will be used for all analyses, and syntax will be used to select and modify cases and variables without saving, to avoid creating several versions of the same dataset. The copy of the master dataset will be saved in the appropriate file format for the program being used for analysis and data visualization (e.g., Stata); multiple copies may be saved if multiple programs are used.

#### Plans for collection, laboratory evaluation, and storage of biological specimens for genetic or molecular analysis in this trial/future use {33}

Dried blood spot will be collected on the first and last days of NRT treatment and on day 7 of NRT treatment. Dried blood spots will determine the progesterone and estrogen levels to confirm the phase of the menstrual cycle and determine cotinine concentration levels to confirm smoking status. Participants will perform the collection procedure independently. Drops of whole blood are collected on filter paper from a finger prick with a single-use lancet following sterilization with isopropyl alcohol. Blood drops are left to dry for at least 4 h or overnight, and the filter paper matrix stabilizes the analytes in the dried blood spot at room temperature [22]. Dried blood spots provided by the participants will be stored at − 80 °C in the freezer at a designated CAMH facility prior to biochemical analysis at a University of Toronto-affiliated laboratory and will be destroyed after they are analyzed.

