**Methods:**

Participants will enroll in an online smoking cessation program providing nicotine replacement therapy (NRT) and behavioral support. We will randomize 1200 eligible individuals to set a target quit date: (1) during the mid-luteal phase, (2) during the mid-follicular phase, or (3) 15–30 days after enrollment with no regard to the menstrual cycle phase (usual practice). Participants will receive a 6-week supply of combination NRT consisting of a nicotine patch plus their choice of nicotine gum or lozenge. Participants will be instructed to start using NRT on their target quit date. Optional behavioral support will consist of a free downloadable app and brief videos focusing on building a quit plan, coping with cravings, and relapse prevention, delivered via e-mail. Smoking status will be assessed via dried blood spot analysis of cotinine concentration at 7 days, 6 weeks, and 6 months post-target quit date.

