### Trial design {8}

The study design is an open-label, parallel-group, superiority randomized controlled trial. Participants will be randomized into three groups in a 1:1:1 allocation ratio: (1) quit smoking during the mid-luteal phase of their menstrual cycle (6–8 days pre-onset of menses), (2) quit smoking during the mid-follicular phase of their menstrual cycle (6–8 days post-onset of menses), or (3) quit smoking 15–30 days post-enrollment with no regard to the menstrual cycle phase (usual practice). All participants will receive 6 weeks of NRT to aid in their quit attempt. The expected duration of the clinical trial is 48 months; we expect participant recruitment and data collection to occur over 27 months. Participants are not required to make any in-person visits; therefore, any potential COVID-19 restrictions are not expected to cause any significant disruptions to our timeline.

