The research team will mail each participant a study kit consisting of a 6-week supply of NRT (patches plus gum or lozenge) and dried blood spot collection kits. Participants who smoke 10 or more cigarettes per day will receive 4 weeks of 21 mg and 1 week each of 14 mg and 7 mg nicotine patches, while those smoking 5–9 cigarettes per day will receive 4 weeks of 14 mg and 2 weeks of 7 mg nicotine patches. Nicotine patches will be pre-organized into weekly packages, requiring the participants to reduce the dosage from 21 mg or 14 mg to 7 mg throughout the 6-week treatment period. All groups will be instructed to collect a dried blood spot and start using their NRT on their target quit date, as well as attempt to be completely abstinent from smoking starting from their target quit date onwards. Dried blood spots will be used to measure blood cotinine levels to confirm participants’ smoking status. Participants will be instructed to apply a new patch every day and use 2 mg nicotine gum or lozenge as needed to curb any urges to smoke. The research team will provide each participant with 2 packs of nicotine gum in which the maximum dosage is 30 pieces a day. These combinations and dosages of NRT have been found most effective for smoking cessation [17].

Participants will also have access to the behavioral support videos and handouts from the time they receive their welcome e-mail until the end of the study. Participants will be asked to complete daily diaries and weekly questionnaires to document tobacco use, NRT use, nicotine craving and withdrawal symptoms, mood, adverse events, and menstrual cycle symptoms via online REDCap surveys. Additional questionnaires will include Patient Health Questionnaire [18] (PHQ-9; weeks 1 and 6), Positive Affect and Negative Affect Schedule – Short Form [19] (PANAS-SF; weeks 1–6), Minnesota Nicotine Withdrawal Scale [20] (MNWS; weeks 1–6), and Perceived Stress Scale 4 [21] (PSS-4; weeks 1–6). Smoking status will be assessed at the end of weeks 1 and 6; those who self-report continuous abstinence from smoking for at least 7 previous days will be asked to collect dried blood spots and mail them within 3 days of collection (for biochemical verification of abstinence). At the end of treatment (week 6), participants will also be asked to complete a study satisfaction survey. Refer to Fig. 1 for a brief overview of the study and to Fig. 2 for a detailed schedule of events.

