### Outcomes {12}

#### Primary outcome

We are primarily interested in the between-group comparison of proportions of biochemically confirmed abstinence, measured through dried blood spots, at 7 days post-target quit date. The trial will be considered successful if the proportion of abstinent participants in either of the groups with a target quit date based on the menstrual cycle phase (follicular or luteal) is significantly higher than in the usual practice group.

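### At day 7 (primary) and week 6, abstinence is confirmed by blood cotinine while all arms are told to use nicotine replacement, with no stated way to separate abstinent users from smokers

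*Protocol article*

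**What the plan says.** All references are to the protocol article.

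- **Endpoint.** Primary outcome, under Outcomes {12}, compares "proportions of biochemically confirmed abstinence, measured through dried blood spots, at 7 days post-target quit date". Primary analysis, under Statistical methods {20a}, carries this into the logistic regressions.
- **Marker.** The Abstract (Methods) says: "Smoking status will be assessed via dried blood spot analysis of cotinine concentration at 7 days, 6 weeks, and 6 months post-target quit date". Section {33} says the spots will "determine cotinine concentration levels to confirm smoking status", alongside the hormone assays that confirm cycle phase.
- **Timing of samples.** Section {33}: "Dried blood spot will be collected on the first and last days of NRT treatment and on day 7 of NRT treatment".
- **Nicotine exposure.** Trial design {8}: "All participants will receive 6 weeks of NRT to aid in their quit attempt". Intervention description {11a} starts NRT on the target quit date and adds: "Participants will be instructed to apply a new patch every day and use 2 mg nicotine gum or lozenge as needed". Patches in week 1 are 21 mg or 14 mg, depending on cigarettes smoked per day. In the last week they are 7 mg for everyone.
- **Who is tested.** Under {11a}, only participants who report at least 7 days of continuous abstinence are asked for a verification spot at weeks 1 and 6.
- **Other relevant data.** All participants are told to collect a spot on the target quit date ({11a}). Daily NRT use or non-use is reported ({11b}, {18a}). Participants may stop NRT ({11b}). Spots are destroyed after analysis ({33}).

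**The concern.** Cotinine is a metabolite of nicotine, whether the nicotine comes from a cigarette, a patch, gum or a lozenge. The day-7 and week-6 samples both fall inside the period of prescribed NRT. A participant who has quit and follows the instructions is therefore expected to have cotinine in her blood on both days. The result reflects NRT use as well as smoking.

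Two kinds of error follow, depending on how the laboratory result is read.

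- A strict reading rejects true abstainers who use their NRT, while those who stopped NRT are easier to confirm.
- A lenient reading accepts some participants who still smoke but report abstinence.

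Either one shrinks the difference that the trial was sized to detect, and the primary comparison is affected directly. Patch strength also differs between day 7 and week 6, and the 6-month sample falls after the supply ends. The error may therefore differ between visits within the single mixed model planned for later time points.

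**Working it through.** **Step 1. Do the test days fall within NRT?** NRT starts on the target quit date and lasts six weeks in all arms. The verification spots are taken on day 7 and on the last day of NRT. Both fall within NRT. The 6-month sample comes after the supplied NRT has ended.

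**Step 2. Does the article say how to read cotinine under NRT?** It gives no cut-off, no rule for comparison with the quit-date spot, no rule that uses the reported NRT use, and no marker independent of NRT. A missing cut-off alone could be left to a laboratory manual. The choice of cotinine as the only named marker during prescribed nicotine treatment is stated in the article itself.

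**Step 3. Reproduce the planned power.** Inputs from Sample size {14}: 1200 participants allocated 1:1:1 (about n = 400 per arm), 25% vs 34% abstinent at day 7, stated power 80%. Primary analysis sets significance at 0.05 without multiplicity adjustment. I assume a two-sided test.

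Power = Φ[(d − 1.96·SE0)/SE1], where d is the difference in proportions, p̄ is their mean, SE0 = √(2p̄(1−p̄)/n) and SE1 = √((p1(1−p1)+p2(1−p2))/n).

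With p1 = 0.25, p2 = 0.34 and p̄ = 0.295: SE0 = 0.03225, SE1 = 0.03209, and (0.09 − 1.96 × 0.03225)/0.03209 = 0.835. Power = Φ(0.835) = 79.8%. A simulation with simple randomization (200,000 runs) gave 79.9%. The stated 80% reproduces.

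**Step 4. Strict reading.** Let q be the share of true abstainers rejected, equal in both arms. The rates become 0.25(1−q) and 0.34(1−q).

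| q (assumed) | Usual practice | Intervention | Power, 400 per arm |
|---|---|---|---|
| 0 | 25.0% | 34.0% | 80% |
| 10% | 22.5% | 30.6% | 74% |
| 25% | 18.8% | 25.5% | 63% |
| 50% | 12.5% | 17.0% | 43% |
| 80% | 5.0% | 6.8% | 19% |

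**Step 5. Lenient reading.** Let f be the share of all non-abstainers counted as abstinent, equal in both arms. The rates become 0.25 + 0.75f and 0.34 + 0.66f, so the difference is 0.09(1−f).

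| f (assumed) | Usual practice | Intervention | Difference (points) | Power, 400 per arm | n per arm for 80% |
|---|---|---|---|---|---|
| 0 | 25.0% | 34.0% | 9.0 | 80% | 402 |
| 5% | 28.8% | 37.3% | 8.6 | 73% | 474 |
| 10% | 32.5% | 40.6% | 8.1 | 66% | 554 |
| 20% | 40.0% | 47.2% | 7.2 | 54% | 744 |
| 30% | 47.5% | 53.8% | 6.3 | 43% | 988 |

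The documents give no value for q or f. The tables show sensitivity and are not a forecast.

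**The case against.** The strongest defence is that the article contains the ingredients for a better reading. The spot gives a concentration and not only a positive or negative result, each participant has her own quit-date level, and NRT use is reported daily. The full protocol, version 1.2 (Trial status), is not shown and may contain a rule. This tempers certainty about how the test will be applied. It does not remove the point, because the article names cotinine alone wherever it names the marker and links none of these data to its interpretation.

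Several stronger readings are tempting and are not supported.

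- *No cut-off could ever work, or the test cannot separate the groups at all.* That depends on how far cotinine levels overlap between abstinent NRT users and smokers, and the documents give no figure for it.
- *Every participant is on NRT at the test.* Participants are supplied and instructed, but may stop. Cotinine remains informative in those who did, and at 6 months in those reporting no nicotine product use.
- *The primary comparison loses most of its signal.* This needs both a strict reading and a large q. Only self-reported abstainers are tested, so a reading that passes everyone amounts to self-report among those who return a spot. The power loss then depends on how many non-abstainers report abstinence.
- *The treatment comparison is biased.* NRT is the same in all arms, and section {11b} expects no systematic difference in discontinuation. The error is probably largely non-differential. It could become differential if NRT use varied with cycle phase.

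**Conclusion.** The concern holds in this form: at day 7 and week 6, cotinine as described does not reliably separate abstinent participants using the supplied NRT from those still smoking, so calling these outcomes biochemically confirmed is not supported. The main consequence is lost power. Under the assumed error rates, the planned 80% falls to between 74% and 19% on a strict reading, or between 73% and 43% on a lenient one. These figures rest on error rates equal across arms, 400 per arm, a two-sided 0.05 test, an unadjusted comparison of proportions and, as in the plan, no allowance for attrition. The 6-month outcome is not affected in participants who report no nicotine product use.

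**What to change.** 1. At day 7 and week 6, do not let cotinine reclassify a participant who reports NRT use. Define both outcomes as self-reported abstinence from the questionnaire, supported by the daily diary, and do not describe them as biochemically confirmed on cotinine alone.
2. Alternatively, if the laboratory can run an NRT-independent marker on the same spots, use that for verification. This must be settled before the spots are analyzed and destroyed.
3. Keep cotinine verification at 6 months among participants reporting no nicotine product use.
4. Show day-7 and week-6 cotinine descriptively only. A comparison restricted to NRT non-users would select on a post-randomization variable.
5. Keep the quit-date spot for the hormone assays.

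**Cost.** Option 1 needs no extra participants or visits. It does require changed outcome definitions in the protocol and registration. Recruitment began on November 30, 2022, so this is a mid-trial amendment. It should be made and registered before anyone sees outcome data by group.

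**Downside.** Self-report in an open-label trial may overstate abstinence. Option 1 removes the strict-reading error but not false reports of abstinence, whose effect on power follows the lenient table with f as the share of non-abstainers who report abstinence. An NRT-independent marker would address both errors, at the price of another assay.

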## Statistical methods

### Statistical methods for primary and secondary outcomes {20a}

#### Primary analysis

To evaluate the primary outcome, we will compare the proportions of biochemically abstinent participants between the groups. Consistent with current practice, and because we expect an advantage over usual practice for only one menstrual cycle phase group, we will compare each intervention arm to usual practice without adjustment for multiplicity. A *p*-value < 0.05 will be considered statistically significant.

We will use logistic regression to test the group differences. As adjustment for prognostically important baseline covariates increases power and decreases bias, we will adjust for age, income, and the heaviness of smoking index (HSI), all of which are known to be meaningfully predictive of successful smoking cessation. We will fit two separate models [26], one for each of our comparisons (i.e., follicular phase group vs. usual practice group and luteal phase group vs. usual practice group).

#### Secondary analyses

To test for a difference between the two intervention arms, we will fit a third model comparing day 7 post-target quit date outcomes in the follicular phase and luteal phase group. To test the group differences at later time points, we will use mixed-effects logistic regression with a random person-level intercept. We will incorporate all follow-ups and all groups into a single model. If within-group change can be captured by a linear slope and an interaction, we will fit a model including group, time, group × time, age, income, and HSI as fixed effects. Otherwise, we will dummy-code time points and interact these with group indicators. In either case, we will derive and test group differences at specific time points using post-estimation procedures.

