### Sample size {14}

We estimate 1200 participants (1:1:1 allocation ratio) to be a realistic sample size, allowing us to achieve sufficient statistical power for the primary outcome analysis. To evaluate power for the primary objective, we ran simulations at various sample sizes by randomly generating data using distributions and coefficients drawn from existing data from the STOP Program. To confirm the final sample, we ran a set of 10,000 simulations. A total analysis sample of 1200 participants allocated in a 1:1:1 ratio using simple randomization will provide 80% power to detect a statistically significant difference for our primary outcome. We anticipate that the proportions quitting successfully on day 7 post-TQD will be 25% in the usual practice group, 34% in one intervention arm, and 25% in the other intervention arm. The effect sizes were calculated without accounting for attrition in the final sample size.

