#### Concealment mechanism {16b}

Randomization of each participant will occur shortly after their enrollment. Participants will not be directly informed of their group assignment; however, they will be provided with a date range for their target quit date to prepare for their quit attempt and the start of the intervention. The allocation sequence will be uploaded to REDCap and will be protected by restricting user rights so it will only be accessible to the study statistician and data manager, who are not involved in recruitment. Therefore, the sequence will be concealed from both participants and unauthorized study staff.

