### Assignment of interventions: blinding

#### Who will be blinded {17a}

This study is open-label. However, the data analysis and outcome adjudication will be blinded.

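### The week-6 and 6-month comparisons let the observed outcomes choose between linear and categorical time, which costs some interval coverage at week 6; visit should be categorical from the start

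*Protocol article*

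**What the plan says.** Under Secondary analyses, the article puts all groups and all follow-ups (day 7, week 6, 6 months) into one mixed-effects logistic model with a random person-level intercept. The coding of time is conditional. "If within-group change can be captured by a linear slope and an interaction, we will fit a model including group, time", together with group × time, age, income and the heaviness of smoking index. The alternative follows: "Otherwise, we will dummy-code time points and interact these with group indicators". Under either coding, group differences at specific time points are then derived by post-estimation. The article states no test, threshold or time scale for the choice.

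The day-7 comparisons, both primary and follicular versus luteal, are separate logistic models and do not use this rule.

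On blinding, section 16b says of the allocation sequence that "it will only be accessible to the study statistician and data manager". Section 17a says that "the data analysis and outcome adjudication will be blinded". Section 17b reveals the identity of the groups only after the primary and secondary analyses are complete.

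**The concern.** Whether within-group change is linear can be judged only from the outcomes, so the model is picked after looking. The standard errors are then computed as if it had been fixed in advance.

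The linear branch also suits the target poorly. With two time parameters per arm and three visits, the fitted week-6 difference borrows from day 7 and month 6. Day 7 is where the plan expects its 9-point effect, and supplied treatment stops at week 6. Whenever the linear branch is kept although the truth is not linear, part of a short-lived early effect is carried into the end-of-treatment estimate. What is at stake is the accuracy of the week-6 secondary result and its interval.

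The blinding passages raise a separate, smaller matter: a reader cannot tell how the analysis stays blinded if the analyst is the statistician who can open the sequence.

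**Working it through.** **Inputs from the article.** 1200 participants, 1:1:1, so about 400 per arm. Day-7 abstinence is expected to be "25% in the usual practice group, 34% in one intervention arm, and 25% in the other intervention arm". Significance is at 0.05. Visits are at about weeks 1, 6 and 26.

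**Assumed inputs.** The article gives no week-6 or 6-month rates and no within-person correlation. The rates below are assumptions, with a latent correlation of 0.75.

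**Step 1: reproduce the plan's figure.** Power for 25% versus 34%, n = 400 per arm, two-sided 0.05:

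z = [0.09 × √400 − 1.96 × √(2 × 0.295 × 0.705)] / √(0.25 × 0.75 + 0.34 × 0.66) = (1.800 − 1.264) / 0.642 = 0.835

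This gives power 0.798, which agrees with the stated 80%. The time-coding point does not affect it.

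**Step 2: what linear time does to visit-specific differences.** Take rates of 34/20/12% against 25/20/12%, so the true differences are 9, 0 and 0 points. A logistic line in weeks gives fitted differences of 5.9, 3.9 and −0.8. A line in visit number gives 7.9, 2.2 and −1.1. If the true difference is 9 points at every visit, either line gives 8.9 to 9.3.

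**Step 3: why the time scale matters.** On the weeks scale, week 6 lies (6 − 1)/(26 − 1) = 20% of the way from first to last visit; on the visit-number scale it lies 50% of the way. Take a phase arm with 34/25/25%. The logits are −0.663, −1.099 and −1.099. The line joining the first and last visits passes week 6 at

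- weeks: 0.8 × (−0.663) + 0.2 × (−1.099) = −0.750, a gap of 0.348 from the true logit;
- visit number: (−0.663 − 1.099)/2 = −0.881, a gap of 0.218.

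The smaller gap is harder to detect, so a lack-of-fit test keeps the wrong line more often. In simulation the line was kept in about 12% of runs in weeks and about half of runs by visit number.

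**Step 4: the rule as written.** Simulation with 400 per arm and marginal logistic fits with robust variance, standing in for the mixed model. The rule was given a definite criterion, a joint 5% lack-of-fit test. The first two rows are the ranges over two scenarios with an effect mainly at day 7: 34/25/25 vs 25/25/25% and 34/25/22 vs 25/24/20%.

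| Scenario and time scale | Week-6 bias, rule (points) | Week-6 coverage, rule |
|---|---|---|
| Mainly day 7, weeks | +0.2 to +0.5 | 90–92% |
| Mainly day 7, visit number | +1.1 to +1.5 | 85–88% |
| Near-linear decline, 34/29/25 vs 25/21/18, weeks | +0.2 | 94% |
| No effect at any visit, weeks | not tabulated | about 95% |

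Categorical time gave about 95%. Repeat runs put the low end of the visit-number row at 84%.

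**Step 5: a second data model.** With random-intercept data (SD 2.0), 34/20/12 vs 25/20/12%, the week-6 test under the rule rejected falsely in 6.5% of runs (weeks) and 15% (visit number), against about 5% with categorical time.

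**The case against.** The strongest reply is that linear time is not imposed: the article uses it only if it fits and names dummy coding otherwise. That stands. A reader might infer that a straight line is forced on the three visits, and so expect a week-6 bias of about 4 points with coverage near 65%. Those figures belong to a model that is always linear, which the plan does not adopt. Under the conditional rule, a clear misfit usually sends the analysis to dummy coding.

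It is also fair that the later rates and the correlation are assumed, that the adverse scenarios have the effect mostly gone by week 6, and that trial success rests on day 7 alone.

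A third reply is that the test, threshold and time scale may sit in an analysis plan that is not shown. Their absence from an article is indeed no fault. But the article does state that observed change decides the coding, and the simulation shows the loss of coverage even when a definite criterion is supplied.

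On blinding, a reader might infer that the promise is false. The documents do not support that. The access in section 16b concerns concealment, no section says who runs the analysis, and section 17b implies masked groups until the results are complete.

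**Conclusion.** The concern holds as a moderate point about secondary outcomes only. A data-driven choice of time coding serves visit-specific comparisons poorly. If the effect is mainly at day 7, week-6 coverage falls from about 95% to 90–92% (weeks) or 85–88% (visit number), with bias of at most about 1.5 points. If decline is near-linear or the effect is constant, little is lost. These sizes rest on assumed later rates, an assumed correlation and marginal fits in place of the planned mixed model. The primary analysis, its power and the day-7 follicular-versus-luteal comparison are unaffected.

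The blinding passages are in tension and need one reconciling sentence. They are not evidence that blinding fails.

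**What to change.** Prespecify visit as categorical with group-by-visit terms and delete the linear branch.

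The cost is one more time parameter per group and some precision if a line would have been right. The week-6 standard error is about √(2 × 0.25 × 0.75/400) = 3.06, roughly 3.0 points, against about 2.6 for a correct linear model. Sample size and primary power do not change.

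Separately, state that the primary and secondary analyses use masked group codes and are run by someone without access to the sequence. Recruitment began in November 2022, so a change of user rights cannot undo access already held. If the study statistician was to run the analysis, a second analyst may be needed.
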